**Clinical success:**

**Diarrhoea:** Will be defined as cessation of watery/abnormally loose stool, and disappearance of visible blood (for children with dysentery) within 48 hours of starting of an effective therapy.

**Pneumonia**: will be defined as disappearance of clinical signs (i.e. crepitations if present) and symptoms of pneumonia/ALRI within 48 hours of starting an effective therapy

1. **Case Definitions**

**Diarrhoea**: Diarrhoea is defined as the passing of liquid or watery stools more than 3 times in previous 24 hours [56].

**Stool consistency:** Stool consistency will be categorized as follows:

1. Watery: That can be poured from one container to another container easily. Like water with no/little attachment to the container.

2. Soft: That cannot be poured from one container to another container easily, like water, but quickly takes the shape of the container.

3. Formed: That retains its shape.

1. **Assessment of dehydration**

Dehydration will be assessed in accordance with the modified WHO guideline as used at the Dhaka Hospital of ICDDR, B[57].

1. **Acute lower respiratory tract infection (ALRI) / Pneumonia: [58]**

In the proposed study, pneumonia would be defined according to the following criteria.

A child presenting with cough or difficult breathing with any of the following:

1. Fast breathing: This will be defined according to age groups.
   1. 6 – 11 months = > 50 breaths per minute
   2. 12 – 59 months = > 40 breaths per minute
2. Crackles on chest auscultation
3. **Grading of ALRI [13]**

- ALRI1- defined as cough and increased respiratory rate (according to age) of the patients.
- ALRI2 - defined as cough and rectal temperature of 38.50C or more at least once in a 24-hour period.

1. **Sign of recovery from pneumonia [58]**

Within 48 hours-sign of improvement: Specific respiratory rate according to age will be decreased.

1. **Severe pneumonia [58]: Will be diagnosed based on the presence of the followings:**
2. Cough
3. Lower chest wall indrawing (the lower part of the chest moves in or retracts when inhalation occurs in a calm child).
4. Fever (may be absent)
5. Lungs auscultation: crackles, and decreased or bronchial breath sounds.
6. **Case Management**

**Management of severe malnutrition:** Would be done according to the protocolized management of severely malnourished children at Dhaka hospital [57]. This protocol is based on WHO guidelines for management of severe malnutrition[59]

**Management of dehydration:** Dehydration will be managed following WHO criteria in malnourished children [57](<http://w3.whosea.org/techinfo/pdf/nutrmanu.pdf> accessed on 12 July,2005 at 1000 hrs). For children with severe dehydration (body weight loss of 10% or greater) initial hydration will be done with intravenous polyelectrolyte solution (“Cholera saline” containing sodium, potassium, chloride and bicarbonate of 133, 13, 98 and 48 mmol/L respectively) in an amount of 20ml/kg in the first hour and 10ml/kg in the second hour; the rest of the estimated deficit (70ml/kg) will be corrected using ORS solution (sodium, potassium, chloride, citrate and glucose [or rice powder] of 75, 20, 65, 10, and 75 [rice powder 40 gm/L] respectively). Calculated total intravenous fluid will be administered as drops per minute (1ml = 60 drops by a ‘micro drip’ or a ‘soluset’). ORS solution would be administered @10ml/kg each hour during the initial 2 hours and then @ 5 ml/kg each hour until full hydration is achieved. The ongoing stool loss will be replaced by administering 5-10 ml/kg of ORS for each watery stool. In the event children are unable to drink ORS solution due to any reason (extreme lethargy, frequent vomiting, and unconsciousness) that would be administered through a NG tube.

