**Study design**

This will be a randomized, double blind, controlled clinical trial examining the effects of daily low dose versus single large dose followed by daily low dose of vitamin A supplementation on the diarrhoea and ALRI/pneumonia morbidities of severely malnourished hospitalized children.

Study site

The study will be conducted at the Dhaka hospital of ICDDR, B. The hospital is located in Dhaka, the capital city of Bangladesh that has a population of over 13 million. Each year, around 100,000 diarrhoeal patients, with and without complications, attend the hospital seeking treatment for their illnesses, and about 6000 of them, mostly under-five children, require admission to the longer stay wards for complications of diarrhoea or presence of other infectious diseases, particularly ALRI/pneumonia and sepsis, and severe malnutrition (45 to 50%).

Inclusion criteria

1. Age 6-59 months
2. Either sex
3. Severe malnutrition as defined by the presence of any of the followings:
   1. Bipedal oedema
   2. Weight (measured after correction of dehydration) for height Z score <-3 of the National Center for Health Statistics (NCHS) reference
   3. Written informed consent of respective parents/ guardians for participation of the children in the study.

Exclusion criteria

1. Failure to obtain consent
2. Received a dose of vitamin A within the last three months
3. History of night blindness or eye signs of vitamin A deficiency
4. Measles or history of measles within last 8 weeks [49]
5. Clinical suspicion of TB (evening rise of temperature, loss of appetite, gradual loss of weight, cough, night sweating) after applying modified Kenneth Jones criteria [50], shock other than due to hypovolaemia or hypoglycaemia, congestive cardiac failure, severe sepsis (hypothermia, tachycardia, tachypnea, hypotension) [51], and seizures disorders
6. Trisomy-21
7. Cerebral palsy
8. Any other known chronic disease (eg. hepatic, renal or congenital disorder) or malignant condition.

Final inclusion in the study

Dehydration would be assessed using a modified WHO guidelines (Dhaka Method)[52] that is routinely practiced at the hospital. Dehydration would be managed using oral or intravenous fluids, as appropriate, following the WHO guidelines. A final diagnosis of acute infection, either diarrhoea or ALRI/pneumonia or both, will be made after the correction of dehydration and patient will be enrolled in the study.

Study Interventions

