There will be two treatment groups: (i) test intervention, and (ii) comparator.

1. Treatment group: Will receive four capsules of vitamin A placebo orally (2 capsules for children aged <12 months) on the day of enrollment plus an oral dose of 5000 IU of vitamin A (in the form of multivitamin drops), and the same oral dose of vitamin A for the next 14 days i.e. throughout their entire nutrition rehabilitation phase in the hospital.
2. Comparator group: Will receive oral mega dose (4 capsules of vitamin A, each containing 50,000 IU i.e. a total of 200,000 IU; 2 capsules for children aged <12 months i.e. a total of 100,000 IU) plus an oral dose of 5000 IU of vitamin A (in the form of multivitamin drops), and the same oral dose of vitamin A for the next 14 days i.e. throughout their entire nutrition rehabilitation phase in the hospital.

A local pharmacutical company (Drug International, Bangladesh) will prepare and supply vitamin A capsules and placebo for the study. One of the investigators will administer the study interventions to the participating children following the randomization schedule at a fixed time of each day, and the date and time of actual administration will be recorded. Randomization will be done by an experienced scientist, not involved in the study in any way, using a block randomization method with variable sizes of blocks between 2 to 6.

Sample size

The sample size of this study has been estimated on expected proportions of clinical success in two groups. Earlier studies have observed 69% and 65% clinical recovery among children suffering from shigellosis and cholera respectively [53, 54], and 60% for pneumonia (personal communication with [name], Kamlapur field site of ICDDR,B) within 48 hours when treated with an effective antimicrobial agent. We assume that the recovery rate would remain same (i.e. 70%) in the high followed by low dose vitamin A group and there would be 15% increase in the rate i.e. 85% in the low dose vitamin A group. Considering 80% power at 5% significance the sample size is estimated as follows:

N = P1 (100-P1) + P2 (100-P2)  F (  ) where P1= 70% and P2 = 85%.

(P1- P2)2

= 118.  = 7.84

Thus the required sample size is 118 in each group, and with an anticipated dropout rate of around 10% the sample size will be 130 children in each of the two treatment groups i.e. a total of 260 children.

Patient recruitment, Clinical and Laboratory Assessments

1. **Patient recruitment**

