   1. Children will be screened for recruitment between 9 am to 4 pm everyday. A trained research assistant will initially screen them. After explaining the study including its aims, procedures, interventions and their possible risks and benefits, rights to refuse participation and withdrawal of consent during study, and confidential handling of information the parents/guardians would require to give consent to enroll their children. The same research assistant will then perform anthropometric measurements including height, weight and mid upper arm circumference, and calculate weight for age, height for age and weight for height percentiles taking National Center for Health Statistics (NCHS) median as the standard. Z-scores will be computed and children with weight for height Z-score less than 3 will be enrolled in the study .
   2. Final enrollment: After rehydration, children will be re-weighed, and final enrollment will be done if weight for height Z-score less than 3 .
2. **Clinical Assessments**
   1. Research assistant will collect the demographic and other data using a pre-designed clinical record form (CRF).
   2. One of the investigators will obtain pertinent medical history and perform through physical examination, and also ensure that the children meet eligibility criteria. All information would be recorded on a pre-designed and pre-tested case report form (CRF).
   3. Randomization: Patient will be randomly assigned to either of the two interventions based on a computer generated randomization table.
   4. During hospitalization data will be collected on the outcome variables as well as relevant clinical information including type and severity of diarrhoea and pneumonia.
   5. All the patients will receive standard treatment as per the hospital’s guidelines.
3. Laboratory assays
   1. **Blood test**s: Blood for retinol and RBP, glucose, complete blood count, serum electrolytes, total protein, albumin and, as measures of infection status, pre-albumin and C-reactive protein (CRP) will be measured after randomization on the admission day. Serum retinol and RBP will also be measured on study day-3 and 15. Any other heamatological test will be repeated if only clinically indicated. . Approximately 3.0 ml of venous blood will be adequate to perform all of the tests.

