**Antimicrobial therapy for infectious illness**

The standard antimicrobial therapy for management of severely malnourished children at the Dhaka hospital of ICDDR,B will be used for management of the study children.

Pneumonia: children will receive parenteral chloramphenicol in a dose of 75-100 mg/kg.day in 4 equally divided doses for the first 2 days followed by an oral formulation in the same dosage for the next 5 days.

If no clinical improvement is observed to occur within 48 hours (i.e. patients remain febrile and or respiratory rate does not come down) or if the clinical condition deteriorates after 24 hours of treatment, chloramphenicol will be replaced by parenteral ceftriaxone to be administered in a dose of 100mg/kg once daily plus gentamicin 1.5 mg/kg parenterally every 8 hours for 7 to 10 days.

Diarrhoea: Children with cholera will be treated with erythromycin administered in a dose of 12.5 mg/kg body weight every 6 hours for 3 days, and those with shigellosis will be treated with 12.5 mg/kg of pivmecillinan every 6 hours for five days.

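### The 48-hour window for both primary outcomes starts at an undefined effective therapy and not at randomisation or the first study dose, which leaves scoring ambiguous and may dilute the comparison

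*Protocol*

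**What the plan says.** - **Success definitions.** Under *Clinical success*, diarrhoea must resolve "within 48 hours of starting of an effective therapy". Pneumonia requires disappearance of signs and "symptoms of pneumonia/ALRI within 48 hours of starting an effective therapy". Neither definition names the therapy or mentions randomisation or the study capsules.
- **Other sections.** The Project Summary gives 48 hours without an origin, and the *Primary outcome* list gives no time at all. *Sample size* takes its planning rates from children recovering "within 48 hours when treated with an effective antimicrobial agent", so background antimicrobial treatment is the natural meaning of effective therapy.
- **Enrolment.** *Final inclusion in the study* says that the diagnosis of infection "will be made after the correction of dehydration and patient will be enrolled in the study". *Patient recruitment* agrees: "After rehydration, children will be re-weighed, and final enrollment will be done". Screening runs from 9 am to 4 pm.
- **Study dose.** The capsules are given on the day of enrolment, and "the date and time of actual administration will be recorded" (*Study Interventions*).
- **Antibiotic change.** *Antimicrobial therapy for infectious illness* replaces the first pneumonia regimen on either of two triggers. One begins "If no clinical improvement is observed to occur within 48 hours"; the other is deterioration after 24 hours. For diarrhoea it names drugs for cholera and shigellosis only.

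**The concern.** A randomised comparison of 48-hour success needs a time zero that is the same for every child, fixed at or before randomisation, and close to the start of the randomised treatment. This one fails in three ways.

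1. **It is not aligned with the intervention.** If background therapy starts first, part of the window passes before the capsules could act. If it starts later, the window runs past 48 hours on the study treatment.
2. **It depends on a later judgement.** Whether a therapy was effective is known only from what happened after randomisation. A child whose first pneumonia regimen failed has, literally, not yet started an effective one.
3. **It may not exist for some children.** If only antimicrobials count, diarrhoea with no listed drug has no start. Rotavirus is an example, and the protocol tests for it on admission.

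Two assessors could follow the text faithfully and score the same child differently. Dilution matters here because the hypothesis is superiority of the low dose, while the statement of relevance says that similar efficacy would have programmatic implications. A diluted null result could be misread as equivalence.

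**Working it through.** **The plan's own figure.** From *Sample size*: 70% against 85%, 80% power, 5% significance, factor 7.84.

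n = [70×30 + 85×15] / 15² × 7.84 = 3375 / 225 × 7.84 = 117.6, so 118 per group.

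This reproduces. With the same unpooled variance, power = Φ(difference / SE − 1.96), where SE = √{[p₁(1−p₁) + p₂(1−p₂)] / 118}. For 70 against 85%, SE = 0.0535 and 0.15 / 0.0535 = 2.80, so power is 80%. The point below concerns a definition, so 118 itself is not in dispute.

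**Illustration 1: therapy starts h hours before the first capsule.** Assumptions, none of them in the documents: constant recovery hazards, and no vitamin A effect before the capsule. The comparator stays at 70%. The low-dose group has the comparator's hazard for h hours and its own for the remaining 48 − h:

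p₂ = 1 − 0.30^(h/48) × 0.15^((48−h)/48)

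| h | Success, comparator vs low dose | Difference (points) | Power at 118 per group |
|---|---|---|---|
| 0 | 70 vs 85.0% | 15.0 | 80% |
| 6 | 70 vs 83.6% | 13.6 | 71% |
| 12 | 70 vs 82.2% | 12.2 | 60% |
| 24 | 70 vs 78.8% | 8.8 | 34% |

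**Illustration 2: the pneumonia clock restarts after an antibiotic change.** The protocol's pneumonia rate is 60%; adding the planned 15 points gives 75%. Suppose that every non-success restarts and succeeds at the same rate as before, so that p becomes p + (1−p)p:

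- 0.60 + 0.40×0.60 = 0.840
- 0.75 + 0.25×0.75 = 0.9375

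Power at 118 per group:

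- without restart: 0.15 / 0.0602 = 2.49, giving 70%
- with restart: 0.0975 / 0.0404 = 2.41, giving 67%

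The difference shrinks from 15 to 9.75 points, but power barely moves because the variance shrinks too. The 118 per group is kept only for comparability; the number of children with pneumonia is not given.

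**What re-anchoring does to the planning rates.** Under the assumptions of illustration 1 with h = 12, take only children still ill at the first dose, scored 48 hours after background therapy began (36 hours after the dose). The rates are 1 − 0.30^(36/48) = 59.5% and 1 − 0.15^(36/48) = 75.9%. At 118 such children per group, power is 78% against 60% when early recoveries are left in. Removing recoveries that precede the study dose therefore restores most of the lost power, but at rates that are not 70 and 85%.

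**The case against.** The strongest case on the other side is that the text does not establish a lag, that the trial is randomised and double blind, and that detailed scoring of antibiotic changes often sits in an analysis plan. Much of this stands, and it limits the point in several ways.

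- **A reader might infer that part of the window always precedes the capsule.** The documents do not show this. Antimicrobials are not timed against the study dose, and treatment that depends on the final diagnosis may start with or after it. What is shown is that the offset is uncontrolled in either direction.
- **A reader might put the lag at 12 to 14 hours from the rehydration rates** (10 ml/kg per hour for 2 hours, "then @ 5 ml/kg each hour until full hydration is achieved"). That is 20 ml/kg in 2 hours, then 50 / 5 = 10 hours, plus 2 hours if the intravenous phase comes first. The 70 ml/kg behind it applies to severe dehydration only, and the proportion of such children is not given. It measures the lag only if rehydration counts as the effective therapy. On that reading, rotavirus diarrhoea does have a time zero, so the two complaints cannot both be pressed.
- **A reader might apply the restart to the 70 and 85% rates.** That gives 91.0 against 97.8% and power of 62%. But the written rule for changing treatment on failure covers pneumonia only. It is triggered by lack of improvement or by deterioration, whereas success requires signs and symptoms to disappear. A child who has improved but still has crepitations is a non-success who is not switched. Even the 67% above restarts too many children.
- **A reader might infer bias towards one arm.** Blinding and randomisation make dilution and ambiguity the expected effects. Changes of antibiotic occur after randomisation and could differ by arm, but nothing in the documents says that they will.

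The appeal to an analysis plan does not remove the point. The protocol does not leave time zero open; it fixes it, and fixes it at an event that is undefined and unrelated to the randomised treatment.

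**Conclusion.** The point holds as a badly fixed endpoint definition. Time zero for both primary outcomes is an unnamed effective therapy, no other section ties it to randomisation or the first dose, and the text does not say how a child whose antibiotic is changed for non-response is scored. The consequence is a primary outcome that cannot be scored reproducibly and a comparison that may be diluted.

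The size is unknown, because the documents give neither the lag nor the success rate after a change of antibiotic. Under the stated assumptions, lag is the larger risk: from about 9 points of power at 6 hours to about 46 at 24 hours. The restart matters less for power (about 3 points at the pneumonia rate) than for the meaning of success, since a treatment failure could be reported as a recovery.

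**What to change.** Reword both definitions under *Clinical success*:

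- Delete *effective* and count 48 hours from the first study dose.
- Assess each illness present at randomisation, with every randomised child who had that illness in the denominator.
- Score a change of antimicrobial made for non-response or deterioration, and death before 48 hours, as non-success.
- Do not score as failure a culture- or susceptibility-directed antimicrobial started without clinical failure.

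Reconcile these definitions with *Antimicrobial therapy for infectious illness* for endpoint scoring only; clinical management does not change.

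The cost is wording in the protocol and the case report form. The dose time is already recorded; the form must also hold the reason for any antimicrobial change. The downside is that observed success may fall below the planning rates, which refer to 48 hours under an effective antimicrobial. *Sample size* should therefore restate its assumed rates on the new time zero and check whether 118 per group still suffices.

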With the above background, we propose a study to examine the effects of daily low dose vitamin A (5000 IU for 15 days) in severely malnourished children, aged 6-59 months, with diarrhoea, with or without pneumonia, and compare that with initial high dose (200,000 IU) followed by a daily low doses (5000 IU for 14 days) of vitamin A in a randomized, controlled clinical trial. All children enrolled in the study would receive the standard care and treatment for their diarrhoea and associated illnesses. Serum concentrations of retinol and retinol binding protein will be measured in study children before randomization, after 48 hours (i.e. on 3rd day) and 14 days later (i.e. on 15th day). The duration of diarrhoea, and proportion of children recovering from pneumonia (return of respiratory rate to normal, and resolution of fever, and ability to eat and drink well) within 48 hours will be the primary outcome measures, and the findings would be correlated with serum retinol and retinol binding protein. We hope that this study might provide valuable information in defining an evidence-based programme for vitamin A supplementation to severely malnourished children.

DESCRIPTION OF THE RESEARCH PROJECT

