One of the investigators will assess study children at least once daily, usually in the morning; however, additional assessments may be performed in the interim if deemed necessary for clinical management. Each child will be weighed every morning, without clothes, to the nearest 0.5 gm using an electronic weighing scale (model 6810; Seca Corporation, Columbia, MD). Height, or recumbent length in children less than 2 years of age, will be measured with a standard height or length board to the nearest 0.1centimeter. MUAC will be measured midpoint between the elbow and the shoulder of the left arm with a non-expanding tape and recorded to the nearest 0.1 cm. Rectal temperatures will be measured 3 times/ day.

1. Morbidity evaluation

Morbidity data such as presence of cough, difficult breathing, fever and other symptoms, and findings of physical examination including pulse and respiratory rates, presence of oedema, mental status (lethargy, irritable, drowsy, obtundation, coma), dehydration status, lower chest wall in-drawing will be recorded. Detailed inquiries will be made about stool frequency, consistency and contents (mucus, blood, undigested food etc).

1. **Discharge from the hospital**: Patients will be discharged after recovery.
2. Definition of recovery from acute phase illness

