**Primary outcome**

1. Resolution of diarrhoea
2. Resolution of ALRI

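### The sign of recovery from pneumonia accepts any fall in respiratory rate, conflicts with two stricter recovery definitions, and the primary ALRI outcome does not say which one applies

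*Protocol*

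**What the plan says.** The protocol describes recovery from pneumonia in three ways and names the outcome in a fourth place.

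- **Sign of recovery from pneumonia** (in the part that opens with *Definition of recovery from acute phase illness*): "Within 48 hours-sign of improvement: Specific respiratory rate according to age will be decreased". Nothing is added on amount, target or counting procedure.
- **Clinical success**, pneumonia: "disappearance of clinical signs (i.e. crepitations if present) and symptoms of pneumonia/ALRI within 48 hours of starting an effective therapy".
- **Project Summary**, where the primary outcome measures are described: "return of respiratory rate to normal, and resolution of fever, and ability to eat and drink well", within 48 hours.
- **Primary outcome**: "Resolution of ALRI", with no definition and no cross-reference.

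The case definition of ALRI/pneumonia requires cough or difficult breathing plus either fast breathing or crackles. Fast breathing is "> 50 breaths per minute" at 6–11 months and "> 40 breaths per minute" at 12–59 months. On assessment, *Daily examination and recordings* says "One of the investigators will assess study children at least once daily, usually in the morning" and allows further assessments for clinical management.

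**The concern.** A criterion met by any fall does not separate recovery from ordinary variation between two counts. A one-year-old whose rate goes from 62 to 61 meets it while still well above 40, so the same child is at once a case and a recovery under the protocol's own definitions.

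Resolution of ALRI is a primary outcome. In a double-blind trial, false recoveries of this kind should arise equally in both arms. They raise both proportions and shrink the difference between them, so power falls and the reported recovery rates are too high. Because the outcome list does not say which definition applies, two assessors could score the same child differently and each could cite the protocol.

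**Working it through.** **1. The plan's own figure.** From *Sample size*: P1 = 70%, P2 = 85%, factor 7.84 (80% power, 5% significance).

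n = (0.70 × 0.30 + 0.85 × 0.15) × 7.84 / 0.15² = 0.3375 × 7.84 / 0.0225 = 117.6, so 118 per group. This agrees with the protocol. With the same unpooled variance, power at 118 is 80.1% (a pooled test gives 79.2%). The sample size arithmetic is not in error.

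**2. Chance of a lower second count with no real change.** The protocol gives no variability for a respiratory count, so the SDs here are assumptions.

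- Two counts around one unchanged rate: P(second < first) = (1 − P(tie)) / 2. With SD 2, ties are 14.0%, giving 43.0%. With SD 6, ties are 4.7%, giving 47.7%.
- Children enter by this route because the first count was high, so regression to the mean adds to this. Simulation kept children whose first count exceeded the cut-off, with count SD 2 to 6 and three assumed distributions of the true rate (mean 58, SD 8, cut-off 50; mean 50, SD 8, cut-off 40; mean 55, SD 6, cut-off 50). It gives 45% to 58%.
- A second set of assumptions (mean excess over the cut-off 6 to 15, between-child SD 8, count SD 3 to 7) gives 46% to 57%.

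About half is therefore stable across these assumptions.

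**3. Effect on the comparison.** Let f be the share of unrecovered children scored as recovered. The observed proportion is p + (1 − p)f, and the difference shrinks by the factor (1 − f). With f = 0.5:

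- High-then-low dose: 0.70 + 0.30 × 0.5 = 85.0%
- Low dose: 0.85 + 0.15 × 0.5 = 92.5%
- Difference: 7.5 points instead of 15
- Standard error at 118 per group: √[(0.85 × 0.15 + 0.925 × 0.075) / 118] = 0.0408
- 0.075 / 0.0408 − 1.96 = −0.12, so power is 45.1% (pooled test 44.5%)
- Needed per group for 80%: 0.196875 × 7.84 / 0.075² = 274.4, so 275

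This treats all 118 per group as ALRI cases scored on the decreased-rate line alone.

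**4. The definitions side by side.** Consider a child with no real change whose count happens to fall.

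| Definition | Can counting noise alone score recovery? |
|---|---|
| Rate decreased | Yes, in about half |
| Clinical success | No: the cough or difficult breathing required at entry must also disappear |
| Project Summary | Only if the child is already afebrile and feeding well, and the noisy count reaches normal (not defined) |

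The first row also cannot sensibly score a child who entered on crackles without fast breathing.

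**The case against.** The strongest reply is that nothing ties the decreased-rate line to the primary outcome. It calls itself a sign of improvement, it follows the case definitions, and it resembles the check for lack of improvement under *Antimicrobial therapy for infectious illness*. *Sample size* rests on clinical success, which is the term defined strictly under *Clinical success*. This stands: a reader might infer that the protocol scores recovery on any decrease, but it does not say so. It is equally silent on excluding that line, whose own heading calls it a sign of recovery.

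Three further inferences are tempting and not supported:

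- **One unconfirmed count decides recovery.** The protocol neither says this nor requires a repeat; assessment is at least daily, with extra assessments allowed.
- **About one unchanged child in ten recovers falsely even under a return to the cut-off.** Assumed SDs of 2 to 6 give 3% to 20%. That range applies only where rate is the sole abnormal component, as for a child who is afebrile and feeding well under the Project Summary. The share of such children is unknown.
- **Noise matters equally whichever definition is used.** The table above shows that it does not.

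Two limits on the 45% figure also stand. The planning rates draw on recovery seen in earlier studies and may already contain some false recoveries. Also, children may enrol with diarrhoea alone, so the ALRI comparison has fewer than 118 per group. With an assumed 59 per group, power is about 50% with no misclassification and 25% at f = 0.5.

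**Conclusion.** The point holds as a badly fixed and conflicting outcome definition. One of three recovery criteria has no threshold and can be met by a child who still satisfies the fast-breathing definition. The three are not equivalent, and the primary outcome list does not select one.

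The size is conditional. If the decreased-rate line alone scored the outcome for every child, false recovery in about half of unchanged children would halve the planned 15-point difference and leave about 45% power at 118 per group. The share rests on an assumed count SD of 2 to 7; the dilution that follows from it is arithmetic. If either stricter definition governs, the loss is much smaller, and the document gives no basis for a figure. The document does not support concluding that the trial as planned has 45% power. The point is worth correcting before scoring begins.

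**What to change.** Reconcile the Project Summary, *Clinical success*, *Sign of recovery from pneumonia* and *Primary outcome* to one definition for scoring the primary ALRI outcome, and refer to it from each place. Specifically:

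- Do not use a decreased rate as a recovery criterion.
- Wherever respiratory rate enters the outcome, require it to be no longer above the age-specific case cut-off (50 at 6–11 months, 40 at 12–59 months). State that a fall leaving it above the cut-off is not recovery.
- Keep the crackles and symptom components, so that children who entered without fast breathing can be scored.
- State whether fever and feeding belong to the definition.

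A repeat count is optional. Under the assumptions used here, requiring two counts at or below the cut-off lowers false recovery on rate alone from about 3–20% to about 1–8%. That gain supposes independent errors, which two counts at one examination may not have.

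This concerns outcome scoring only and leaves the treatment-change wording under *Antimicrobial therapy for infectious illness* untouched. The cost is wording in four places. The downside is a somewhat lower reported 48-hour recovery proportion in both arms.
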